### 2.12. Statistical analysis methods

All data will be analyzed according to the intentionality analysis and will follow the protocol analysis statistics. Statistical descriptions will be used to compare the baseline information. The mean ± standard deviation or median (interquartile range) will be used to express the measurement data, and rates or percentages will be used for count data. For measurement data, a *t* test or Mann–Whitney *U* test will be used to detect differences between the groups. The Chi-squared test will be used to analyze the count data.

All data will be analyzed using SPSS 23.0 (IBM Corporation, Armonk, NY) software, and *P* < .05 (2-sided) will be considered a statistically significant difference.

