**Discussion::**

Currently, no prospective controlled data exist regarding the efficacy and safety of carotid stenting in the acute phase. Previously, we had developed an ECASES stent placement system for acute carotid artery occlusion. The present study will evaluate the efficacy and safety of ECASES in a randomized, double-blind prospective study and clarify its guiding significance in acute atherosclerotic carotid artery occlusion surgery.

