We believe that assessment and decision making should be individualized and objective for each patient and cannot be generalized. In our previous work, we summarized a decision evaluation system, Emergent Carotid Artery Stent placement decision Evaluation System (ECASES), for stent placement decisions in atherosclerotic acute carotid artery occlusion. The system is divided into 3 parts: bleeding risk score, ischemia risk score, and an individualized decision-making system that can specifically and quantitatively assess a patient’s risk of intracranial hemorrhage and ischemia and make individualized treatment recommendations.

Therefore, this study aimed to further evaluate the efficacy and safety of ECASES through a randomized, double-blind, prospective controlled study to clarify its guiding significance in acute atherosclerotic carotid artery occlusion surgery.

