### 2.11. Sample size estimation

Assuming a rate of good neurological function in both the study and control groups (180 d) of not less than 51%, a noninferiority threshold Δ=–10%, a sample ratio of the study and control groups of 1:1, a unilateral test level (α = 0.025), a total certainty of 80%, and a 5% loss rate, the total sample size required is 202 patients and 101 patients in each group.

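### The only stated rule for the harm counts is a two-sided difference test, which cannot support a statement that ECASES is no more harmful; a risk difference with its 95% interval could bound the excess

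*Protocol article*

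**What the plan says.** Safety appears beside efficacy in the statement of purpose. The Introduction says that "this study aimed to further evaluate the efficacy and safety of ECASES", and the Discussion part of the Abstract repeats it: "The present study will evaluate the efficacy and safety of ECASES in a randomized, double-blind prospective study".

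Section 2.8 lists the harms as secondary outcomes: hemorrhage events (graded, with a symptomatic category), cerebral edema in four grades, new infarction on diffusion-weighted imaging, and reocclusion of the responsible vessel.

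Section 2.12 assigns tests by data type. For counts it says "The Chi-squared test will be used to analyze the count data", and the threshold for all data is P < .05: "2-sided) will be considered a statistically significant difference".

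Section 2.11 holds the only margin, "a noninferiority threshold Δ=–10" percent, and ties it to the rate of good neurological function. It concludes that "the total sample size required is 202 patients and 101 patients in each group". No expected rate, margin or power is attached to any harm. Section 2.10 provides a data and safety monitoring committee.

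**The concern.** Section 2.11 plans the trial as a noninferiority comparison. In that setting the favourable safety message is that ECASES causes no more hemorrhage, infarction or reocclusion than the operator's judgement. The stated rule does not address that question. A two-sided chi-squared test asks whether the groups differ, and failing to reject is not evidence that an excess is small.

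The Introduction describes stenting as a trade between hemorrhage and reocclusion, so these harms are central to judging a decision aid of this kind. If the report gave only a non-significant P value for an uncommon event, a reader could take it as reassurance although the data allowed a material excess. Testing the primary outcome against its own margin would not change this, because that margin does not reach the harms.

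**Working it through.** **Inputs from the article.** 101 patients per group (2.11); 5% loss, so 0.95 × 101 = 95.95, about 96 evaluable; chi-squared test, two-sided 0.05 (2.12).

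**Inputs assumed.** The control rate of symptomatic hemorrhage. The article gives none, so a range of 2% to 15% is shown. A doubling is used as the example of clear harm.

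**The plan's own figure.** There is none for safety. The 202 in section 2.11 is for the efficacy margin, and it does not follow from the inputs stated there:

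n = (1.960 + 0.842)² × 2 × 0.51 × 0.49 / 0.10² = 393 per group; 393 / 0.95 = 414 per group; 828 in total.

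That is a separate matter. The calculations below take 101 per group as given.

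**Step 1. Chance of missing a doubling.** By normal approximation, with control rate p₁, ECASES rate p₂ = 2p₁ and mean rate p̄:

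power = Φ{[(p₂ − p₁) − 1.96 √(2p̄(1 − p̄)/n)] / √([p₁(1 − p₁) + p₂(1 − p₂)]/n)}

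For 5% against 10%, n = 101: Φ[(0.050 − 1.96 × 0.0371)/0.0369] = Φ(−0.61) = 0.27, so the test misses 73% of the time.

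Exact enumeration of two binomials (uncorrected Pearson test, counting only rejections in the direction of harm) gives:

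| Control rate → doubled rate (assumed) | Missed, n = 101 | Missed, n = 96 |
|---|---|---|
| 2% → 4% | 89% | 89% |
| 3% → 6% | 85% | 85% |
| 5% → 10% | 73% | 74% |
| 10% → 20% | 48% | 50% |
| 15% → 30% | 27% | 29% |

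For a commoner event, a 10-point excess is missed 63% of the time from 20% and 68% from 30% (n = 101).

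**Step 2. What a non-significant result can hide.** Take 12/101 on ECASES and 5/101 on control (illustrative counts).

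- Difference: 0.1188 − 0.0495 = 0.0693.
- Test: pooled rate 17/202 = 0.0842; z = 0.0693 / √(0.0842 × 0.9158 × 2/101) = 1.77; P = 0.076.
- Wilson limits: 0.0693 to 0.1963 (ECASES) and 0.0213 to 0.1107 (control).
- Newcombe upper limit: 0.0693 + √[(0.1963 − 0.1188)² + (0.0495 − 0.0213)²] = 0.152.
- Newcombe lower limit: 0.0693 − √[(0.1188 − 0.0693)² + (0.1107 − 0.0495)²] = −0.009.

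The 95% interval runs from −0.9 to +15.2 points, although the stated rule would report no significant difference. With equal counts, 5/101 in each group, the same formula gives ±6.7 points.

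**Step 3. Would a larger sample settle it?** For 80% power to detect a doubling, the two-sided test needs 749 per group at 3% against 6%, 435 at 5% against 10%, and 199 at 10% against 20%. Even the 414 per group that section 2.11's own inputs require would fall short of 435. The practical remedy is therefore in how the harms are reported.

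**The case against.** The strongest reply is that nothing here is misstated. A chi-squared test is an ordinary choice for proportions and does not preclude confidence intervals. Section 2.12 also says that rates or percentages will be given, so the event rates by group will be visible. Interval methods often sit in an analysis plan, which is not shown. The harms are secondary, no power is claimed for them, and low power for uncommon events is common in trials of this size.

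Most of this stands, and it limits the point. Three stronger readings are tempting, and the article supports none of them:

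- *That the article treats P > .05 as proof of safety.* It says only what counts as a significant difference and sets no rule for a null result.
- *That safety rests on hemorrhage and reocclusion alone.* Edema, new infarction and neurological worsening are also outcomes, and a monitoring committee is in place.
- *That a doubling of symptomatic hemorrhage would almost certainly be missed.* The miss rate depends wholly on an assumed control rate and falls to about 27% at 15%. The definition of symptomatic hemorrhage in section 2.8 joins its alternatives with an *or*, which makes the expected rate harder to place.

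The reply does not remove the mismatch between a stated aim and a stated rule. The article does fix a method for these outcomes, and that method cannot deliver a no-more-harmful conclusion. If the analysis plan already contains intervals, section 2.12 need only be brought into line with it.

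**Conclusion.** The point holds as a cheap improvement of minor to moderate weight. Safety is a declared aim, and the one analysis rule stated for the harm counts can detect a difference but cannot support a statement that ECASES is no more harmful. At 101 per group a true doubling of symptomatic hemorrhage would be missed between about 89% and 27% of the time for assumed control rates from 2% to 15%. The range rests on those assumed rates, on the uncorrected Pearson test and on full follow-up; at 96 per group the figures rise by at most about 2 points. A reader might infer that the trial must be enlarged for safety or that it is set to declare ECASES safe by default. Neither follows: the article claims no power for these outcomes and states no criterion for declaring safety.

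**What to change.** In section 2.12, for symptomatic intracranial hemorrhage, any hemorrhage, new infarction and reocclusion:

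- report the risk difference (ECASES minus control) with a 95% confidence interval, by Newcombe or Miettinen-Nurminen;
- keep the chi-squared P value as descriptive;
- state that any safety conclusion will rest on the upper confidence limit, quoted as the largest excess not excluded, and that P > .05 will not be read as evidence of safety.

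The cost is a few sentences and standard calculations on data already to be collected, with no extra patients, visits or imaging. The downside is a more modest safety statement: the report will have to say that an excess of up to so many points is not excluded.

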1)Inclusion criteria.•Age 18–80 years old, regardless of sex.•Preoperative National Institutes of Health Stroke Scale (NIHSS) score ≥ 6.•An Alberta Stroke Program Early Computed Tomography Score (ASPECTS) ≥ 6 based on magnetic resonance imaging diffusion-weighted imaging (MRI-DWI) sequences.•The time from onset to the expected start of endovascular treatment is ≤ 24 hours, with patients between 6 and 16 hours meeting the inclusion criteria for the DAWN study and the DEFUSE 3 study, and patients between 16 and 24 hours meeting the inclusion criteria for the DAWN study.•Pre-stroke modified Rankin Scale (mRS) score of 0–1.•Life expectancy ≥ 2 years.•Patients and their families agree to the endovascular treatment and study protocol and sign an informed consent form.2)Exclusion criteria.•Patients with combined intracranial hemorrhage confirmed by CT or MRI.•Patients with a combination of severe renal insufficiency (creatinine level > 264 µmol/L), respiratory and circulatory instability, severe coagulation dysfunction (international normalized ratio > 3.0, or partial thromboplastin time more than 3 times the normal value), and other contraindications to interventional procedures.•Patients with preexisting neurological(pre-stroke mRS score ≥ 2, stroke attack with epilepsy, combined with intracranial tumors) or psychiatric disorders could confound the results.•Uncontrollable hypertension is defined as a systolic blood pressure > 185 mm Hg and diastolic blood pressure > 110 mm Hg.•Platelet count < 50,000/µL.•Blood glucose < 2.78 mmol/L or > 22.20 mmol/L.•Patients who cannot undergo cranial MRI.•Patients deemed unsuitable for study participation by other investigators.3)Exclusion and discontinuation criteria: Patients may withdraw at any stage of the study.•Voluntary withdrawal, where informed consent is withdrawn, and patients are free to withdraw from the study at any time without prejudice to subsequent treatment.•Missed patient visits.•Any safety reasons (adverse events) as perceived by investigators.•Other cases where researchers decide whether it is appropriate for patients to withdraw from the study.4)Preoperative evaluation.•General information: Age, sex, time of onset, past medical history, and stroke risk factors, including blood pressure, blood glucose, blood count, coagulation series, and electrocardiogram.•Neurological function assessment: NIHSS and mRS scores will be used as tools for neurological function evaluation and completed by senior physicians.•Imaging evaluation: All patients undergo preoperative cranial CT to exclude intracranial hemorrhage and massive cerebral infarction. All patients will undergo cranial MRI to clarify the diagnosis and extent of acute cerebral infarction and will then be scored based on MRI-DWI sequences with reference to the ASPECTS scoring system. The presence of large infarcts in the basal ganglia area (large infarcts: >2/3 of the basal ganglia area) will also be assessed. All the patients will undergo MRA, CTA, and/or DSA to confirm the presence of atherosclerotic carotid occlusion. In some patients (6–24 hours after onset), CT perfusion imaging or nuclear perfusion imaging will be performed to assess the semidark bands.

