
### 2.3. Randomized grouping and blinding method

Randomized grouping method: Pass software will be used to randomize the study subjects into the study and control groups. The study subjects will be numbered, and random numbers will be generated using the pass software functions Transform-Compute (calculate new variables) - Rv.Uniform (uniformly distributed random number function). Transform-Rank Cases will be applied to generate a random number order.Blinding: The study will be double-blind, blinded to the patient and investigator, and neither the patients nor investigators will know the subject grouping throughout treatment and follow-up. The randomization grouping results will be maintained by a dedicated person (stenting protocol selection decision maker), who is a nontreatment/non-follow-up participant who is aware of the patient’s grouping assignment (study or control group) and maintains patient and investigator confidentiality.

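### The article names only unadjusted group comparisons, although prognostic baseline measures are collected before surgery, so the primary comparison may give up precision

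*Protocol article*

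**What the plan says.** **Analysis (Protocol article, section 2.12).** For measurement data, a t test or Mann-Whitney U "test will be used to detect differences between the groups". For categorical data, "The Chi-squared test will be used to analyze the count data". The only use given to baseline data is descriptive: "Statistical descriptions will be used to compare the baseline information". No regression, covariate or stratified analysis appears anywhere in the article.

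**Baseline data (section 2.2, preoperative evaluation).** The list opens with "General information: Age, sex, time of onset, past medical history, and stroke risk factors". Stroke severity and disability are also scored before surgery: "Neurological function assessment: NIHSS and mRS scores will be used as tools for neurological function evaluation and completed by senior physicians". Imaging covers everyone: "All patients will undergo cranial MRI to clarify the diagnosis and extent of acute cerebral infarction", and patients "will then be scored based on MRI-DWI sequences with reference to the ASPECTS scoring system".

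**Allocation (section 2.3).** Uniform random numbers are drawn and then ordered: "Transform-Rank Cases will be applied to generate a random number order". No stratification or minimisation factor is named.

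**Outcome and planning figures (sections 2.8 and 2.11).** The primary outcome is mRS and NIHSS at 90 days. The sample size assumes 51% good function in both groups, a −10-point noninferiority margin, one-sided α of 0.025, 80% power and 5% loss, and gives 101 per group.

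**The concern.** When baseline variables carry information about outcome, an analysis that uses them estimates the treatment difference more precisely than one that does not. Several candidates are already collected here, and one primary measure, NIHSS, has its own preoperative value. A t or Mann-Whitney test on the 90-day score leaves that value unused. As described, allocation does nothing to balance these variables.

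Precision is scarce in this trial. At the planned size, the unadjusted interval for the difference in good function is wider on each side than the noninferiority margin. A gain that needs no extra patients or measurements should not be left out of the stated analysis. It also has to be specified in advance, because covariates chosen after an imbalance has been seen invite a data-driven result.

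**Working it through.** **Inputs.** From section 2.11: 51% good function in both arms, margin 10 points, one-sided α 0.025, 101 per arm, 5% loss. Evaluable per arm: 101 × 0.95 ≈ 96, or 192 in total. Section 2.11 labels the 51% as a 180-day rate; I apply it at 90 days as an assumption. R², the share of outcome variance explained by baseline variables, is not in the documents. I assume 0.04 to 0.30.

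**The plan's own figure.** With z values of 1.960 and 0.842:

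n per arm = (1.960 + 0.842)² × 2 × 0.51 × 0.49 / 0.10² ≈ 393

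Allowing for 5% loss this is 414 per arm, 828 in total. The stated 202 is not reproduced. That is a separate problem, but it limits what adjustment can achieve.

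**Unadjusted precision.**
- Standard error = √(2 × 0.51 × 0.49 / 96) = 0.0722
- 95% half-width = 1.96 × 0.0722 = 14.1 points
- Noninferiority power at equal rates = Φ(0.10/0.0722 − 1.960) = 28%

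**Adjusted precision.** Multiply the variance by (1 − R²). The half-width is then 14.14 × √(1 − R²), the equivalent number evaluable is 192/(1 − R²), and the power is Φ(1.386/√(1 − R²) − 1.960).

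| Assumed R² | Half-width (points) | Equivalent evaluable total | Power at equal rates |
|---|---|---|---|
| 0 (unadjusted) | 14.1 | 192 | 28% |
| 0.04 | 13.9 | 200 | 29% |
| 0.15 | 13.0 | 226 | 32% |
| 0.30 | 11.8 | 274 | 38% |

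**Check of the approximation.** The proposed analysis (a logistic model standardised to a risk difference) was simulated with 96 per arm, 51% good outcome, one baseline score and 4,000 runs per setting. The ratio of adjusted to unadjusted variance was 0.96 for a weak predictor (AUC 0.63), 0.87 at AUC 0.70, 0.79 at AUC 0.77 and 0.71 at AUC 0.81. The ends of this range match variance reductions of about 4% and 30%, so the (1 − R²) rule is adequate here.

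**Ninety-day NIHSS.** Adjusting for baseline NIHSS multiplies the variance by 1 − ρ². For an assumed baseline correlation of 0.3 to 0.6 the factor is 0.91 to 0.64.

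**What adjustment cannot do.** For the half-width to reach 10 points, 1 − R² must equal (10/14.14)² = 0.50, so R² must be 0.50. To reach 80% power at equal rates, the trial would still need about 393 × 0.96 = 377.3 (378) evaluable per arm at R² 0.04, or 393 × 0.70 = 275.1 (276) at R² 0.30, against 96 available.

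**The case against.** The strongest reply is that covariate choice belongs to an analysis plan that is not shown, and that section 2.12 is a generic list by data type. It ties no test to the primary outcome and does not exclude adjustment. Likewise, section 2.3 names no strata but does not say there are none. This is fair as far as it goes. However, the article does state a method for comparing the groups, and on a plain reading it covers the outcomes. The point is about improving that stated method.

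A reader might also infer more than the documents support:

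- **That the unadjusted tests are biased or invalid.** They are not. Chance imbalance is already allowed for in their type I error. For a risk factor present in half of patients, the chance of a 10-point or larger imbalance is about 16% (2 × [1 − Φ(0.10/√(0.5/101))] = 0.155). That is a reason to want adjustment, not a flaw in the test.
- **That strong predictors are documented.** Section 3 links infarct size and site to haemorrhage, and functional recovery to vessel patency and collaterals. It gives no predictive strength for age, NIHSS, ASPECTS or onset time. Entry at ASPECTS 6 or above, and the added selection of later-window patients, may weaken two of these. Pre-stroke mRS of 0–1 leaves almost no spread.
- **That baseline severity is ignored throughout.** Section 2.8 uses preoperative NIHSS to define a secondary outcome (improved, worsened or stable).
- **That power would rise from 80% to about 90%.** That needs a true 61% versus 51%, which the article never states. Section 2.11 gives one rate for both groups.
- **That the gain should be counted on the 202 enrolled.** The half-widths and powers rest on 192 evaluable patients, so the equivalent total must use the same base.
- **That adjustment rescues the noninferiority comparison.** Over the assumed range the half-width stays above 10 points and power stays below 40%.

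**Conclusion.** The point holds as a question of efficiency. The article states only unadjusted comparisons, the relevant baseline values are already collected, and no stratification is described. Any prognostic value in baseline NIHSS or age would be gained at almost no cost.

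The direction is firm but the size is not. Over the assumed R² of 0.04 to 0.30 the benefit runs from negligible to equivalent to about 82 more evaluable patients (274 − 192). The figures rest on 96 evaluable per arm, 51% good function in both arms at 90 days, and the (1 − R²) variance rule. The change is worth making, but nothing in the trial is invalid without it, and it does not replace a correction of the sample size.

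**What to change.** 1. State the binary definition of good neurological function at 90 days. Section 2.8 gives the scales but no cut-off, and a risk difference cannot be analysed until this is settled.
2. Prespecify the primary comparison as a marginal risk difference with 95% confidence interval, standardised from a logistic model with group, baseline NIHSS, age, DWI-ASPECTS and onset-to-treatment time. Compare the lower limit with the −10-point margin. An adjusted odds ratio would not match a margin set in percentage points.
3. Analyse 90-day NIHSS with adjustment for baseline NIHSS.
4. Keep the chi-squared, t and Mann-Whitney comparisons as sensitivity analyses.
5. If allocation is in fact stratified, say so and include the strata in the model.

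The cost is a few sentences of plan text, a routine model and the outcome definition in item 1. The covariates are already collected and no extra patients or visits are needed. The choice should be fixed before outcome data are seen by group.

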### 2.8. Study outcomes

Primary outcome: Neurological functional status at 90 days postoperatively

Patient neurological functional status will be assessed by mRS and NIHSS scores.

Secondary outcomes.

Changes in neurological function are classified as improved (postoperative NIHSS score decrease ≥ 4 points compared with preoperative), worsened (postoperative NIHSS score increase ≥ 4 points compared with preoperative), or stable (postoperative NIHSS score change < 4 points).Hemorrhage events: For the classification of bleeding events, we refer to ECASS II.^[9]^ Hemorrhagic events were classified according to the clinical and CT criteria. Hemorrhagic infarction 1 (HI1) was defined as small petechiae along the margins of the infarct, and hemorrhagic infarction 2 (HI2) as confluent petechiae within the infarcted area but no space-occupying effect.

parenchymal hemorrhage (PH1) as blood clots in 30% or less of the infarcted area with some slight space-occupying effect, and parenchymal hemorrhage (PH2) as blood clots in more than 30% of the infarcted area with a substantial space-occupying effect. Symptomatic intracranial hemorrhage was defined as blood at any site in the brain on the CT scan (as assessed by the CT reading panel, independent of the assessment by the investigator), documentation by the investigator of clinical deterioration, adverse events indicating clinical worsening (e.g., drowsiness, increase of hemiparesis), or a decrease in the NIHSS score of 4 or more points.

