Cerebral edema: According to postoperative CT results, edema is classified into 4 conditions: no edema, mild edema (focal edema up to one-third of the hemisphere), moderate edema (focal edema greater than one-third of the hemisphere), and severe edema (edema with midline shift).^[10]^ Signs of focal edema are defined as narrowing of the cerebrospinal fluid space, for example, effacement of the cortical sulci or ventricular compression.^[11]^Modified treatment in cerebral infarction (mTICI) grading: The mTICI grading will be assessed based on DSA of the responsible vessel at the end of the procedure to evaluate the effectiveness of surgical revascularization.New cerebral infarction: Postoperative MRI-DWI sequences showed a new cerebral infarction (compared with the preoperative).Reocclusion of the responsible vessel: A responsible artery with an immediate postoperative mTICI classification ≥ 2b and a CTA, MRI, and/or DSA examination within 90 days postoperatively, suggesting artery reocclusion, will be defined as reocclusion of the responsible vessel.

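### Section 2.12 has no rule for ordered categories, so the graded secondary outcomes would by the natural reading get a chi-squared test that ignores order and loses power if the effect follows the order (minor).

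*Protocol article*

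**What the plan says.** Section 2.12 sets out two classes of data and one rule for each.

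- Measurement data are summarised by mean and standard deviation or median and interquartile range. The sentence that begins "For measurement data, a" gives them a t test or Mann–Whitney U test.
- Of the other class it says that "rates or percentages will be used for count data", and then that "The Chi-squared test will be used to analyze the count data".

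There is no third class for ordered categories, no ordinal or trend version of the chi-squared test is named, and no test is tied to a named outcome. The significance rule is P "< .05 (2-sided) will be considered a statistically significant difference".

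Section 2.8 defines four secondary outcomes on ordered scales:

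- "Changes in neurological function are classified as improved", stable or worsened, by a 4-point NIHSS cut;
- hemorrhage, graded HI1, HI2, PH1, PH2;
- edema: "edema is classified into 4 conditions: no edema, mild edema", then moderate and severe;
- mTICI grade at the end of the procedure.

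The remaining secondary outcomes (new infarction, reocclusion) and the symptomatic-hemorrhage component are yes/no.

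**The concern.** A grade such as edema is categorical and would be tabulated as percentages, so it meets the plan's own description of count data. Mann–Whitney does appear in the plan, but only for measurement data, so its presence does not settle the matter.

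The Pearson chi-squared test gives the same answer however the columns are ordered. With k grades it spreads the evidence over k − 1 degrees of freedom, and its P value carries no direction. If one treatment strategy shifts patients steadily towards better or worse grades, a test that uses the order finds this more often with the same patients. The trial has 101 patients per arm, and these four outcomes hold much of its secondary evidence on efficacy and safety. Information that will be collected anyway would be partly set aside.

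**Working it through.** **The plan's own figure.** None exists for these outcomes: the article gives no power, expected distribution or effect for any of them. Its only sizing statement, that "the total sample size required is 202 patients and 101 patients in each group", belongs to the primary noninferiority comparison. It is used here only for the arm size.

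**Inputs from section 2.11.** 101 per arm, with "a sample ratio of the study and control groups of 1:1"; 5% loss, so 101 × 0.95 ≈ 96 evaluable per arm. **From section 2.12:** two-sided 0.05.

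**Assumed inputs.** The category distributions, the common odds ratio, a level for no hemorrhage (making five), and the number of mTICI levels (five or six).

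**Step 1. A check that needs no distribution.** A 1-df ordinal test with 80% power at two-sided 0.05 has noncentrality λ = (1.960 + 0.842)² ≈ 7.85. If the chi-squared test has the same λ but more degrees of freedom, its power is P(noncentral χ² > critical value):

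| Levels | df | Critical value | Chi-squared power | Loss from 80% |
|---|---|---|---|---|
| 3 | 2 | 5.99 | 70.9% | 9 |
| 4 | 3 | 7.81 | 64.5% | 16 |
| 5 | 4 | 9.49 | 59.5% | 20 |
| 6 | 5 | 11.07 | 55.5% | 24 |

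**Step 2. One case by hand.** Four levels, 101 per arm, reference 40/30/20/10%, common odds ratio 2.0.

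- Reference cumulative odds are 0.667, 2.333 and 9. Doubled, they are 1.333, 4.667 and 18. The shifted distribution is 57.1/25.2/12.4/5.3%.
- Chi-squared: λ = n Σ (p₁ − p₂)²/(p₁ + p₂) = 101 × 0.0670 = 6.77. With 3 df the power is 57.4%.
- Mann–Whitney, by the proportional-odds approximation: V = (N/12)(1 − Σ p̄³) = (202/12)(1 − 0.1403) = 14.47. Then z = ln 2 × √14.47 = 2.637, and the power is Φ(2.637 − 1.960) ≈ 75.1%.

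The gap is about 17 to 18 points.

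**Step 3. Simulation.** 20,000 trials per scenario, 101 per arm, Pearson chi-squared against the tie-corrected Mann–Whitney test. Cells show chi-squared / Mann–Whitney power in percent, with the gap in points in brackets.

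| Assumed reference distribution | OR 1.25 | OR 1.75 | OR 2.0 |
|---|---|---|---|
| 3 levels, 50/30/20 | 10.4 / 13.1 (3) | 42.6 / 52.9 (10) | 59.8 / 70.0 (10) |
| 4 levels, 40/30/20/10 | 9.7 / 14.1 (4) | 39.2 / 56.4 (17) | 57.1 / 73.7 (17) |
| 5 levels, 60/15/10/10/5 | 7.9 / 12.2 (4) | 28.2 / 47.8 (20) | 42.0 / 65.0 (23) |
| 6 levels (assumed mTICI scale) | 7.8 / 13.7 (6) | 33.2 / 58.0 (25) | 48.7 / 76.0 (27) |

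Two other five-level distributions gave gaps of 21 to 23 points at OR 2.0. At 96 per arm the powers are generally a point or two lower and the gaps are nearly the same. At OR 3 the gap narrows again, to about 3 to 5 points for three or four levels, because both tests are then near their ceiling.

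**Step 4. Type I error.** At OR 1 both tests reject in about 4 to 5% of trials.

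**Step 5. Shifts that do not follow the order.** At 101 per arm the ranking reverses:

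- 50/30/20 against 60/10/30: chi-squared about 93%, Mann–Whitney about 8%.
- 40/30/20/10 against 50/15/15/20: chi-squared 78%, Mann–Whitney 6%.

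**The case against.** **The assignment is inferred.** Section 2.12 never says that edema or mTICI will be tested by chi-squared, and matching each secondary outcome to a test is ordinary content of an analysis plan that is not shown here. That stands as a limit on the claim: a reader might infer that the plan explicitly assigns these outcomes to chi-squared, and it does not. The point survives because the article does not leave the matter blank. It states a two-class rule, and under that rule graded percentages fall on the chi-squared side.

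**The size is not in the documents.** A reader might want one figure for the power lost, say 10 to 18 points. That range fits three or four levels with a mid-size effect and nothing wider. With a small effect the loss is a few points. A small effect is quite possible, since the two arms may often be recommended the same treatment; the article gives no figure for that.

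**Chi-squared has a use.** It would be wrong to say that it brings no benefit. Step 5 shows that it can detect patterns a rank test misses. The introduction describes stenting as trading reocclusion against hemorrhage, so improved and worsened NIHSS classes could both rise. That is a fair objection for NIHSS change. It is weaker for a single scale such as edema or mTICI, because the trade-off runs between outcomes and not within one.

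**Some of these outcomes may be dichotomised.** Section 2.8 already uses an mTICI cut at 2b in defining reocclusion. Chi-squared suits any such yes/no version.

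**Conclusion.** The point holds as a minor one. By the natural reading, four ordered secondary outcomes would be compared by a test that ignores their order, and a more suitable test is already named in the same section. If the effect follows the order, the loss at 96 to 101 per arm is roughly 2 to 6 points of power at a common odds ratio of 1.25. At 2.0 it is about 10 points for three levels, 17 for four and 23 to 27 for five or six. Every one of these figures rests on assumed distributions and effects.

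It would go too far to infer that results from the stated rule would be invalid or biased. Both tests hold their 5% level, the four outcomes are secondary, and no power is claimed for them. The reported percentages would also show direction, even though the P value does not. Only efficiency is at stake.

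**What to change.** Add one sentence to section 2.12: ordered categories (NIHSS change class, hemorrhage grade, edema grade, mTICI grade) are compared by the Mann–Whitney U test, a linear-by-linear trend test or proportional-odds regression with a common odds ratio and 95% confidence interval. Name which of these applies, so that the choice is not made after the data are seen. Keep chi-squared for yes/no outcomes: symptomatic hemorrhage, new infarction, reocclusion, and mTICI or mRS if dichotomised.

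Tabulate all categories by arm for each ordered outcome. This covers the one real cost of the change, which is lower sensitivity to differences that do not follow the order; a simultaneous rise in improved and worsened patients would still be visible in the table. No extra data or patients are needed, and Mann–Whitney is already in the plan.
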